### Grouping and allocation concealment

Patients meeting the eligibility criteria will be randomized to either the Group CHO or the Group CTRL. The carbohydrates beverage Outfast® (Yichang Humanwell Pharmaceutical Co., Ltd., China) used in the study, is isotonic with osmotic pressure of 280–320mmol/L and PH of 3.8–4.3. Patients in Group CHO will orally consume CHO 355ml containing 50 g of carbohydrates 8–12 h before operation (20:00–24:00 the evening before operation). In order to improve adherence to intervention protocol, patients in the Group CHO will be asked to return the empty beverage bottle to the investigator after drinking the beverage. The Group CTRL will consume no food or drink 12 h before operation (20:00 the evening before operation). Based on the random numbers generated by the computer, qualified patients will be randomized to the Group CHO or Group CTRL the day before surgery. The random number list will be kept in the hand of a dedicated person who will assign participants to Group CTRL or Group CHO according to the random numbers. The surgeons, anesthesiologists, ICU staff, nurses, outcome assessors, data collectors, and data analysts will be blinded to the grouping. Unblinding is permissible when patients suffer from gastric acid reflux and aspiration.

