### Statistical analysis

Modified intention-to-treat analysis is adopted to analyze the data. If the operation of an enrolled patient is canceled due to special circumstances such as fever, the random number will be reserved to him/her until the end of the trial. If the patient whose operation is canceled contemporarily is operated later before the end of the trial, he/she will be assigned to the Group CTRL or Group CHO according to the early-assigned random number. If the patient who doesn’t undergo the operation as planned is not operated before the end of the trial or whose operation is rescheduled to a later time of the day instead of the first operation at 8’oclock, he/she will be excluded from the trial and extra random number will be generated to enroll enough patients to the prespecified sample size.

The primary endpoints, homeostasis model assessment (HOMA) of IR, will be compared between the two groups at several fixed time after surgery. In addition, overall postoperative IR will be assessed via area-under-curve of HOMA (AUC_HOMA_) and AUC_HOMA_ will be compared between the two groups. The secondary endpoints, postoperative IR-related mediators, will be compared between the two groups primarily at the first morning after surgery. In the exploratory study, in-hospital outcomes as listed in the following part of the study endpoints will be compared between the two groups. Normal distribution of continuous variables will be tested using the Shapiro-Wilks test. Continuous variables will be presented as mean ± standard deviation if the variables follow a normal distribution, otherwise median and interquartile range. Categorical variables will be presented as number and percentage. Missing data will be managed via multiple imputation. Continuous variables with normal distribution will be compared by Student’s *t*-test between the groups. Continuous variables with skewed distribution will be compared by Mann-Whitney *U* test. We will compare categorical variables with the *χ*^2^ test or Fisher’s exact test. The Spearman rank correlation test will be utilized to assess the correlation between continuous variables.

The analysis will be performed by a dedicated data analyst who is masked to subjects’ group allocation. All the tests in the present study are two-tailed and *P*<0.05 is considered statistically significant. All analyses will be performed with R 4.0.4 (R Foundation for Statistical Computing, Vienna, Austria).

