### Sample size calculation

The primary outcome is the postoperative IR assessed *via* HOMA of the function of islet β cell (HOMA-β). Previous literature [18] showed that the HOMA-β of the CHO group tended to be higher than that of the F group-β (87% *vs*. 47.5%). In the present study, the test power was set to 0.80, two-sided α was set to 0.05, and the dropout rate was set to 0.1. It was estimated that a total of 62 patients with 31 patients in group CHO and 31 patients in group C would be enrolled.

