## Study endpoints

### Primary endpoints

The primary endpoints are postoperative HOMA-β and HOMA-IR. HOMA score is a mathematical model that can reflect the balance between liver glucose output and insulin secretion, and it has been previously demonstrated that it has a strong correlation with clamp-measured total glucose disposal, the gold standard of assessing IR [19].

The calculation formulas of HOMA-β and HOMA-IR are as follows:

$$\textrm{HOMA}-\upbeta \%=\left[20\times \textrm{fasting}\ \textrm{insulin}\ \left(\textrm{mu}/\textrm{L}\right)\right]/\left[\textrm{fasting}\ \textrm{blood}\ \textrm{glucose}\ \left(\textrm{mmol}/\textrm{L}\right)-3.5\right]\%$$$$\textrm{HOMA}-\textrm{IR}=\left[\textrm{blood}\ \textrm{insulin}\ \left(\textrm{mu}/\textrm{L}\right)\times \textrm{Blood}\ \textrm{glucose}\ \left(\textrm{mmol}/\textrm{L}\right)\right]/22.5$$

The HOMA-β is expressed as percentage, and its normal value is 100%. The HOMA-IR is expressed without unit, and its normal value is 1. With the increase of IR, the HOMA-β will be lower than normal and the HOMA-IR will be higher than normal.

The baseline HOMA-β and HOMA-IR will be acquired at admission. And then these two HOMA scores will be sequentially measured before anesthesia induction, immediately after surgery, the first morning after surgery (POD1), POD2, POD 3, and POD 5 (Fig. 1)

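### Admission HOMA is collected but not used: the primary comparison is an unadjusted two-sample test, which gives up precision by an amount that depends on an unstated correlation

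*Protocol article*

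**What the plan says.** All references are to the protocol article.

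- **Endpoint and baseline (Primary endpoints).** "The primary endpoints are postoperative HOMA-β and HOMA-IR". The same section adds that "The baseline HOMA-β and HOMA-IR will be acquired at admission", followed by samples before induction, right after surgery, and on postoperative days 1, 2, 3 and 5.
- **Comparison (Statistical analysis).** The HOMA endpoints "will be compared between the two groups at several fixed time after surgery", and AUC_HOMA is compared between the groups as well.
- **Tests (Statistical analysis).** "Continuous variables with normal distribution will be compared by" Student's t-test. "Continuous variables with skewed distribution will be compared by Mann-Whitney" *U*. The abstract names the same two tests. No covariate, change score or model appears in either place.
- **Allocation (Grouping and allocation concealment).** "Based on the random numbers generated by the computer, qualified patients will be randomized" the day before surgery. Stratification on baseline HOMA is not described. The drink is taken that evening, so the admission sample precedes it and the pre-induction sample follows it.

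**The concern.** The admission value measures the primary endpoint itself, on the same scale and before treatment. It is often the strongest available predictor of the postoperative value. Patients arrive on tablets, insulin or both (Blood glucose monitoring and management), so a wide spread at admission is plausible, though the protocol gives no figure for it.

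A two-sample test leaves all of that predictable variation in the error term. In a trial of 62 patients with nominal 80% power, two things are at stake:

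- power that could be had without further patients or samples;
- protection if the arms turn out to differ at baseline. With no adjustment named in advance, one added after the imbalance is seen would be data-driven.

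**Working it through.** **Inputs from the protocol (Sample size calculation).** "two-sided α was set to 0.05"; "the test power was set to 0.80"; 31 patients per arm; dropout 0.1; HOMA-β 87% against 47.5%, a difference of 39.5 points.

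**Inputs assumed.** The SD and the correlation ρ between admission and postoperative HOMA are not given. The SD is back-solved, and ρ is taken over 0 to 0.7.

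**Step 1: the plan's own figure.** The total of 62 cannot be reproduced, because no SD is stated. Evaluable patients per arm are 31 × 0.9 = 27.9, taken as 28. With a two-sample t-test (54 degrees of freedom), 80% power at 28 per arm needs d = 0.762, so the implied SD is 39.5 / 0.762 = 51.8 points. This is an assumption, not a protocol figure.

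**Step 2: power with adjustment.** Adjusting for the admission value multiplies the error variance by 1 − ρ², so the effective standardised difference is d / √(1 − ρ²). I used the noncentral t distribution with 53 degrees of freedom (one is spent on the covariate) and multiplied the variance by 1 + 1/(56 − 4) = 1.019 for estimating the slope. The noncentrality is [0.762 / √(1 − ρ²)] × √(28/2) / √1.019. Adjusted and unadjusted tests are on the same scale.

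| ρ | 1 − ρ² | d / √(1 − ρ²) | Power, adjusted | Unadjusted |
|---|---|---|---|---|
| 0 | 1.00 | 0.762 | 79.2% | 80.0% |
| 0.2 | 0.96 | 0.778 | 80.8% | 80.0% |
| 0.3 | 0.91 | 0.799 | 82.8% | 80.0% |
| 0.5 | 0.75 | 0.880 | 89.3% | 80.0% |
| 0.7 | 0.51 | 1.067 | 97.3% | 80.0% |

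At a smaller true effect of 0.5 SD, unadjusted power is 45.1%. Adjusted power is 47.9%, 55.6% and 72.2% at ρ = 0.3, 0.5 and 0.7.

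In sample-size terms, adjustment at ρ = 0.5 is worth 28 / 0.75 ≈ 37 patients per arm.

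**Step 3: chance imbalance.** The baseline difference between arms has standard error √(2/28) = 0.267 SD, so its 95% range is ± 1.96 × 0.267 = ± 0.52 SD. It exceeds 0.3 SD in about 26% of trials and 0.5 SD in about 6%.

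Given an imbalance of b SD, the unadjusted estimate shifts by ρb SD, and its conditional standard error is 0.267 × √(1 − ρ²). For b = 0.5:

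| ρ | Shift (SD) | Shift in HOMA-β points (× 51.8) | Conditional type I error |
|---|---|---|---|
| 0.3 | 0.15 | about 8 | 7.5% |
| 0.5 | 0.25 | about 13 | 12% |
| 0.7 | 0.35 | about 18 | 18% |

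Example at ρ = 0.5: the critical difference is 0.524, the conditional standard error is 0.267 × 0.866 = 0.231, and (0.524 − 0.25) / 0.231 ≈ 1.18, an upper tail of about 12%. For b = 0.3 the conditional error stays between 5.0% and 5.5% across the same correlations.

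**The case against.** **The two-sample test is valid.** Over repeated randomisation it is unbiased and holds its 5% error, and chance imbalance is already in its standard error. This stands. A reader might infer that the planned analysis is biased, or that a baseline difference carries over in full to the result. The document supports neither: only the fraction ρ of the imbalance (in SD units) carries over, and the conditional error is clearly raised only for large imbalances, which are uncommon.

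**The size rests on figures that the protocol does not give.** This also stands. The effect in SD units is back-solved from the HOMA-β figures, and ρ is unknown. The section on blood glucose management provides for insulin boluses and infusion, and for intravenous glucose, after surgery. Both act directly on the two quantities in the HOMA formulas and could lower ρ. At ρ = 0.2 the gain is under one point.

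**Part of an apparent gain can come from the log scale.** If HOMA is skewed, setting a log-scale adjusted model against the planned raw-scale procedure mixes two changes. In simulation with log-normal data (28 per arm, an assumed log SD of 0.6, d = 0.762), the planned procedure gave 77–78% power and an unadjusted t-test on logs 79–80%. So 2–3 points come from the logs alone. The figures above compare like with like.

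**The test sentences are generic, and a fuller analysis plan may exist.** This stands only in part. The sentences cover all continuous variables, but no other method for comparing them is named, and the abstract repeats them. The article states a choice here; it does not leave a blank.

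**Conclusion.** The point holds as a matter of efficiency. The protocol collects a pre-treatment value of its primary endpoint and names a primary comparison that ignores it.

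Under the assumptions above, adjustment gains roughly 1, 3, 9 and 17 points of power at correlations 0.2, 0.3, 0.5 and 0.7, and loses under one point if the correlation is zero. That the adjustment is absent is certain from the text; how much it costs is not. The trade still favours adjustment, because the possible loss is negligible and the possible gain is material for a trial of this size. It is a recommended improvement and does not invalidate the planned test.

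**What to change.** For each HOMA endpoint treated as primary (HOMA-β, HOMA-IR and their AUC), replace the two-sample test with a linear model of the postoperative value on arm and the admission value of the same measure. Use the log scale for both if the measure is skewed. Report the adjusted difference, or the geometric mean ratio on the log scale, with its 95% CI.

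- Use the admission value only. The pre-induction sample is taken after the drink and may already carry a treatment effect.
- Do not change which endpoint is primary as part of this edit. The sample size section rests on HOMA-β while the endpoint section names both measures; that is a separate matter.
- A covariate for preoperative insulin treatment is optional, and only if it is recorded at baseline. The data collection section mentions medical history but does not list it.

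The cost is a wording change, made before unblinding, and one degree of freedom. No further patients, samples or visits are needed.

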### Sample size calculation

The primary outcome is the postoperative IR assessed *via* HOMA of the function of islet β cell (HOMA-β). Previous literature [18] showed that the HOMA-β of the CHO group tended to be higher than that of the F group-β (87% *vs*. 47.5%). In the present study, the test power was set to 0.80, two-sided α was set to 0.05, and the dropout rate was set to 0.1. It was estimated that a total of 62 patients with 31 patients in group CHO and 31 patients in group C would be enrolled.

## Study endpoints

### Primary endpoints

The primary endpoints are postoperative HOMA-β and HOMA-IR. HOMA score is a mathematical model that can reflect the balance between liver glucose output and insulin secretion, and it has been previously demonstrated that it has a strong correlation with clamp-measured total glucose disposal, the gold standard of assessing IR [19].

The calculation formulas of HOMA-β and HOMA-IR are as follows:

$$\textrm{HOMA}-\upbeta \%=\left[20\times \textrm{fasting}\ \textrm{insulin}\ \left(\textrm{mu}/\textrm{L}\right)\right]/\left[\textrm{fasting}\ \textrm{blood}\ \textrm{glucose}\ \left(\textrm{mmol}/\textrm{L}\right)-3.5\right]\%$$$$\textrm{HOMA}-\textrm{IR}=\left[\textrm{blood}\ \textrm{insulin}\ \left(\textrm{mu}/\textrm{L}\right)\times \textrm{Blood}\ \textrm{glucose}\ \left(\textrm{mmol}/\textrm{L}\right)\right]/22.5$$

The HOMA-β is expressed as percentage, and its normal value is 100%. The HOMA-IR is expressed without unit, and its normal value is 1. With the increase of IR, the HOMA-β will be lower than normal and the HOMA-IR will be higher than normal.

The baseline HOMA-β and HOMA-IR will be acquired at admission. And then these two HOMA scores will be sequentially measured before anesthesia induction, immediately after surgery, the first morning after surgery (POD1), POD2, POD 3, and POD 5 (Fig. 1)

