## Methods and analysis

### Objectives

The trial is designed to assess the effects of preoperative CHO in T2DM patients undergoing OPCAB. The main hypothesis is that preoperative CHO has advantages in improving postoperative IR and promoting postoperative recovery in T2DM patients undergoing OPCAB. The primary objective is to determine the efficacy of preoperative CHO in improving postoperative IR. The secondary objective is to assess the postoperative level of potential IR-related mediators including biochemical parameters, inflammatory mediators, and stress reaction. In the explorative study, the effects of preoperative CHO on postoperative recovery will be investigated. Postoperative recovery could be assessed via postoperative clinical outcomes such as nausea or vomiting, perioperative myocardial injury or infarction, chest tube drainage, mechanical ventilation time, ICU length, and hospital stay.

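### HOMA-β, an index of β-cell function, is powered as the measure of insulin resistance, and the stated rule for reading it fails whenever insulin drives the change

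*Protocol article*

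**What the plan says.** The Objectives section sets the target: "The primary objective is to determine the efficacy of preoperative CHO in improving postoperative IR".

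The Sample size calculation section takes postoperative IR as the primary outcome but measures it through "HOMA of the function of islet β cell (HOMA-β"), and sizes the trial on that score alone: 87% with CHO against 47.5% with fasting, power 0.80, two-sided α 0.05, 10% dropout, 31 per group.

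The Primary endpoints section names two scores: "The primary endpoints are postoperative HOMA-β and HOMA-IR". It prints both formulas, gives normal values ("The HOMA-β is expressed as percentage, and its normal value is 100"%; "The HOMA-IR is expressed without unit, and its normal value is 1"), and adds the reading rule: "With the increase of IR, the HOMA-β will be lower than normal and the HOMA-IR will be higher than normal".

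The Statistical analysis section says: "The primary endpoints, homeostasis model assessment (HOMA) of IR, will be compared between the two groups at several fixed time after surgery". It adds an area under the HOMA curve without saying which score the curve is drawn from.

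**The concern.** The objective concerns resistance to insulin. The powered score is one that the protocol itself describes as β-cell function. The two are tied together only by the reading rule, which treats a higher HOMA-β as less IR. If that rule is not generally true under the protocol's own formulas, a higher HOMA-β is not evidence of less IR.

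At stake is the direction of the main conclusion. A significant rise in HOMA-β with CHO would be read, under the rule, as improved IR. The same blood samples could give a higher HOMA-IR, which the rule reads as more IR. The score that matches the objective, HOMA-IR, has no power statement.

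**Working it through.** **Inputs.** From Primary endpoints, with I = insulin (mU/L) and G = glucose (mmol/L): HOMA-β (%) = 20·I/(G − 3.5) and HOMA-IR = I·G/22.5. From Sample size calculation: HOMA-β 87% against 47.5%. From Blood glucose monitoring and management: a target of 7.8–10 mmol/L, used here only to choose example values. Insulin values not derived from these are illustrative.

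**The plan's own figures.** The normal values reproduce: I = 5 and G = 4.5 give 20·5/1 = 100% and 5·4.5/22.5 = 1. The total of 62 cannot be reproduced, because no SD is stated. With 31 × 0.9 ≈ 28 evaluable per arm, 80% power for a difference of 39.5 points implies an SD of about 52 to 53 points, or a standardised difference of about 0.75–0.76. Treating 87% and 47.5% as proportions gives a total of 48, or 58 with continuity correction, not 62.

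**Does the rule follow from the formulas?**

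- Insulin fixed, glucose rises: I = 10, G from 8 to 10. HOMA-β goes from 200/4.5 = 44.4 to 200/6.5 = 30.8. HOMA-IR goes from 80/22.5 = 3.56 to 100/22.5 = 4.44. The rule holds.
- Glucose fixed, insulin rises: G = 8, I from 10 to 20. HOMA-β goes from 44.4 to 400/4.5 = 88.9 (read as less IR). HOMA-IR goes from 3.56 to 160/22.5 = 7.11 (read as more IR). The rule fails.

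This is general. Both formulas have I as a factor, so at any fixed glucose above 3.5 mmol/L the two scores rise and fall together, whereas the rule needs them to move in opposite directions.

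**The planning effect at equal glucose.** Solve I = HOMA-β·(G − 3.5)/20, then compute HOMA-IR:

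| G in both arms | I at 47.5% | I at 87% | HOMA-IR at 47.5% | HOMA-IR at 87% |
|---|---|---|---|---|
| 7.8 | 10.21 | 18.70 | 3.54 | 6.48 |
| 8 | 10.69 | 19.57 | 3.80 | 6.96 |
| 10 | 15.44 | 28.27 | 6.86 | 12.57 |

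The ratio is 87/47.5 = 1.83 in every row.

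**When is HOMA-IR not worse with CHO?** With HOMA-β at 87 (CHO) and 47.5 (control), this requires 87·G₁(G₁ − 3.5) ≤ 47.5·G₀(G₀ − 3.5), where G₁ is CHO glucose and G₀ control glucose. For G₀ = 7.8, 9 and 10 the limits on G₁ are about 6.4, 7.2 and 8.0. CHO glucose must be about 1.4, 1.8 and 2.0 mmol/L lower.

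**The case against.** The rule is not simply false. When glucose drives the difference, the two scores behave as stated. At constant insulin, glucose of 10 in controls and 7.05 with CHO gives the whole planned ratio (6.5/3.55 = 1.83), and HOMA-IR is then about 30% lower with CHO (7.05/10 = 0.705). Both primaries would agree. This stands: the fault is that the rule carries no condition.

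HOMA-IR is already a named primary endpoint, and the wording in Statistical analysis can be read as covering both scores. Fasting glucose and insulin are secondary endpoints, so a disagreement would be visible to a careful reader. Which score takes precedence could be settled in an analysis plan that is not shown. This stands in part. An analysis plan cannot, however, make the reading rule agree with the formulas beside it, and it does not alter which score the trial was sized on.

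A reader might go further and infer that the planned effect must come from more insulin, since glucose inside 7.8–10 mmol/L can raise HOMA-β by at most 6.5/4.3 = 1.51. By the same reasoning, the best case for CHO would lower HOMA-IR by only about 5% (6.48 against 6.86). The documents do not support either inference. The 87% and 47.5% come from a cited study whose glucose values are not given. In this trial 7.8–10 is a target, not a bound: in the ICU scheme insulin starts above 10 and glucose is given only below 5.6. With the planned HOMA-β values, control glucose of 10 and CHO glucose of 5.6, CHO insulin is 87·2.1/20 = 9.1 and HOMA-IR is 2.27 against 6.86, about 67% lower.

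**Conclusion.** The point holds. HOMA-β is named and powered as the measure of IR although the protocol describes it as β-cell function, and the unconditional reading rule is not valid under the protocol's own formulas when insulin drives the change. A HOMA-β rise of the planned size is compatible with a HOMA-IR 1.83 times as high (equal glucose), with an unchanged one (CHO glucose about 1.4 to 2.0 mmol/L lower), or with a clearly lower one (glucose difference larger still). HOMA-β alone therefore cannot answer the primary question.

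The factor 1.83 should not be read as a forecast that IR will worsen by 83%. It assumes equal glucose in both arms and treats each arm as one typical patient, so it shows direction and does not estimate group means. The protocol gives no expected glucose by arm. Discordance is possible, not certain. The text still needs correcting, because following it as written could report higher insulin as improved IR.

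**What to change.** - Make HOMA-IR, with lower values better, the primary measure of IR in Statistical analysis, Sample size calculation and Primary endpoints, and state that the area under the curve is that of HOMA-IR.
- Move HOMA-β to the secondary endpoints, labelled β-cell function.
- Delete the statement that HOMA-β falls as IR rises.
- State that a difference in HOMA-β will not be read as a change in IR.

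No new data are needed, since both scores come from the same insulin and glucose samples. The change is nevertheless more than wording. The 80% power at 62 patients applies only to HOMA-β, and the protocol gives neither a HOMA-IR difference nor its SD. Either drop the 80% claim for the primary endpoint or take an SD of HOMA-IR from a cited source and state the difference detectable with 62 patients. With about 28 evaluable per arm and a *t*-test on a normally distributed outcome, that is roughly 0.76 SD. If this difference is too large to be useful, the sample size itself has to be reconsidered. Trial status says enrolment had not begun at submission; the change should be dated and made before any comparison by group.
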